### Economic analysis

TASMINH2^20^ resulted in a 5.4 mm Hg reduction in BP in self-management compared with usual care which was cost-effective with £1.6k per QALY for men and £4.9k for women. Thus if HOME BP results in the hypothesised difference of 5 mm Hg, then using the same cost-effectiveness model, it will be highly cost-effective—unless of course the costs are much greater. The intervention cost in TASMINH2 was £105, which included the BP monitor, tele-monitoring connection and training costs (see table 2 in Kaambwa *et al*^50^). Key differences between the interventions in HOME BP and TASMINH2 have to do with the use of behavioural techniques in the former, including guidance about lifestyle change and support in making such changes as well as recommendations to change medications with recording of whether such changes were made and further reminders if not. HOME BP thus tests the intervention as delivered digitally and the additional value of behavioural support in self-management. To facilitate costing of the behavioural add-ons to self-management, the costing of the intervention in HOME BP as far as possible will separate these elements.

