### Study aims and research questions

The primary aim of the HOME BP trial is to assess the feasibility, acceptability, effectiveness and cost-effectiveness of adding the HOME BP intervention (comprising the HOME BP online DI, self-monitoring, medication titration and lifestyle interventions with nurse support) into primary care for the self-management of hypertension in comparison to usual care.

Main research question:
Does the HOME BP intervention to assist self-monitoring and self-management of uncontrolled hypertension result in greater control of SBP after 1 year?

Secondary research questions:
Does the HOME BP intervention to assist self-monitoring and self-management of uncontrolled hypertension result in greater control of SBP and diastolic blood pressure (DBP) after 6 months and DBP after 1 year?Is the HOME BP intervention more cost-effective than usual care in managing poorly controlled hypertension in primary care?

Process analysis research questions:
Which factors are related to patient engagement and adherence to HOME BP?Which factors are related to patient medication adherence and uptake of recommended medication titrations?Does the inclusion of lifestyle change choices and behavioural support result in engagement with lifestyle change?Is the HOME BP intervention acceptable to patients when integrated into routine practice?What are patient and healthcare practitioner views and experiences of the HOME BP intervention and its addition into primary care for the self-management of poorly controlled hypertension?

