## Methods and analysis

### Study design and setting

The HOME BP intervention for the self-management of high BP consists of the integrated patient and healthcare practitioner HOME BP online DI, BP self-monitoring, health professional directed and supervised titration of antihypertensive medication and user-selected lifestyle modifications, for people with uncontrolled essential hypertension. The HOME BP study is a pragmatic, randomised controlled trial comparing the HOME BP intervention with optional nurse support to a control group receiving usual hypertension care within a UK primary care setting.

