#### Randomisation

Participants will be randomised in a 1:1 ratio to receive either usual care or the HOME BP intervention with optional nurse support using the HOME BP online system. Minimisation will be used taking into account participants' baseline SBP, age, diabetes status and practice. Patients are randomised to the optimal group 80% of the time. Any random numbers the minimisation routine might need will be computer generated, therefore bypassing study team involvement.

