### HOME BP intervention

The HOME BP intervention consists of HOME BP online (for patients and healthcare professionals), BP self-monitoring, medication titration procedures and optional behavioural support. Each of these components is described below, guided by the TIDieR checklist where possible.^37^ The intervention was developed using a theory-based, evidence-based and person-based approach,^38^ which is fully described elsewhere (article in submission).

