### Usual care

Patients allocated to usual care will have access to the information provided in the Blood Pressure UK patient leaflet for hypertension through HOME BP online. They will receive routine hypertension care, with appointments and medication changes made at the GP's discretion.

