#### Economic analysis plan

A within trial analysis will estimate cost per unit reduction in SBP, the primary outcome, with adjustments in that outcome as described in the ‘Statistical analysis’ section, including subgroups. Costs will include those due to the intervention, as well as those due to changes in medication, use of other relevant NHS resources and any costs borne by patients such as in diet and lifestyle. NHS and societal costs will be estimated and uncertainty explored in sensitivity analyses. To facilitate analysis of the difference between the intervention in HOME BP and that of self-management, the components and the cost of the intervention in HOME BP will be compared with that of TASMINH2.

These short-term results will provide input to a long-term cost-effectiveness model, based on that developed for TASMINH2, updated by subsequent work as relevant. Since these studies all show reductions in BP as cost reducing or highly cost-effective, this modelling will address the cost-effectiveness of the HOME BP-intervention versus usual care but also of the addition of the behavioural/digital element relative to paper-based self-management without that element. The HOME BP trial will collect data on numbers and types of antihypertensive prescriptions between arms.

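### The economic section says the trial tests the added value of behavioural support, but two arms (whole package against usual care) cannot identify it

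*Protocol article*

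**What the plan says.** All references are to the protocol article.

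- **Economic analysis.** After listing how HOME BP differs from TASMINH2, the earlier self-management trial, the section concludes: "HOME BP thus tests the intervention as delivered digitally and the additional value of behavioural support in self-management". It adds that the behavioural add-ons will be costed separately as far as possible.
- **Economic analysis plan.** The components and cost of HOME BP will be compared with those of TASMINH2. A long-term model based on the one built for TASMINH2 will address HOME BP against usual care, and also "the addition of the behavioural/digital element relative to paper-based self-management without that element".
- **Randomisation.** "Participants will be randomised in a 1:1 ratio to receive either usual care or the HOME BP intervention with optional nurse support".
- **Study design and setting.** The trial is described as "comparing the HOME BP intervention with optional nurse support to a control group receiving usual hypertension care within a UK primary care setting".
- **HOME BP intervention.** The package consists of "HOME BP online (for patients and healthcare professionals), BP self-monitoring, medication titration procedures and optional behavioural support".
- **Usual care.** Controls can see a patient leaflet online. "They will receive routine hypertension care, with appointments and medication changes made at the GP's discretion".

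**The concern.** To test what behavioural support adds to self-management, a trial must compare self-management with it and self-management without it. This trial has no second group of that kind. The first half of the disputed sentence, on the intervention as delivered digitally, is sound if read as the whole package against usual care. The second half claims a property that the design lacks.

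The Economic analysis plan then sets a modelling aim on the same contrast. That result could be read as a product of the randomised trial, although its key input is a comparison between trials. The article does not call it indirect or non-randomised. The introduction itself cites evidence both ways on whether behavioural support improves on titration alone, so readers will look to this trial for an answer. The Dissemination section also foresees later changes of delivery mode without re-evaluating the behavioural content.

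**Working it through.** **1. What the design identifies.** Write S for the effect of self-management alone against usual care, and B for what the behavioural/digital element adds. The trial estimates the package effect, S + B. With one randomised contrast and two unknowns, B can be obtained only by bringing in S from elsewhere. Separate costing gives the added cost of the element, but not its added effect, and a cost-effectiveness ratio needs both.

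**2. Whether data within the trial can help.** The Statistical analysis section plans process analyses that relate support uptake to outcomes. Support is optional in the intervention arm, so users and non-users select themselves. These analyses do not give a randomised estimate of B.

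**3. Whether TASMINH2 supplies S cleanly.** By the Economic analysis section's own account, the two interventions differ in behavioural techniques and lifestyle support. They also differ in medication-change recommendations, the recording of whether changes were made, and reminders. A difference between the trials would mix all of these. The same section says that the TASMINH2 intervention cost covered a tele-monitoring connection, whereas the reference in the Economic analysis plan is paper-based. If TASMINH2 is that reference, the two descriptions need reconciling.

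**4. The plan's own figure.** Inputs from Sample size consideration: difference 5 mm Hg, SD 17, power 90%. Alpha is not stated; two-sided 0.05 is assumed.

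n per group = 2 × (1.96 + 1.2816)² × 17² / 5² = 243, against 244 stated.

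With 15% dropout, 244 / 0.85 = 287.06, stated as 287 per group and 574 in total. The figure reproduces, and it serves package against usual care only.

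**5. Precision of a cross-trial estimate of B.**

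SE of the HOME BP effect = 17 × √(2/244) = 1.54 mm Hg.

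The TASMINH2 standard error is not in the document, so a range is assumed. SE of the difference = √(1.54² + SE_ext²).

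| Assumed external SE | SE of difference | 95% half-width (1.96 × SE) |
|---|---|---|
| 1.0 | 1.84 | 3.6 mm Hg |
| 1.54 | 2.18 | 4.3 mm Hg |
| 2.0 | 2.52 | 4.9 mm Hg |

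If the estimated added benefit were 2 mm Hg (chosen for illustration), the interval would run from 2 − 3.6 = −1.6 to 2 + 3.6 = 5.6 at best, and from 2 − 4.9 = −2.9 to 2 + 4.9 = 6.9 at worst.

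**6. Effect of baseline adjustment.** The primary analysis adjusts for baseline BP, so 1.54 is probably too large. As a limiting case, set the HOME BP standard error to zero. The external error alone then gives 1.96 × 1.0 = ±2.0 to 1.96 × 2.0 = ±3.9 mm Hg. None of these intervals allows for bias from differences between the trials.

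**The case against.** The strongest defence is that nothing confirmatory rests on the sentence. The main research question, sample size, primary outcome and primary analysis all concern package against usual care, and the only economic research question asks about cost-effectiveness against usual care. This stands, and it limits the severity.

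The second defence is that decision models often take comparators from outside the trial, and that the method may be set out in a fuller protocol or health-economic plan that is not shown. The article names TASMINH2 only for components, cost and the base model, and it promises sensitivity analyses of uncertainty in the costs. So the absence of a method for the indirect comparison is not itself the finding, and TASMINH2 as the source of the comparator effect is an inference. But no further plan can make a two-arm trial test one component of its package.

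Third, the interval widths rest on an assumed external standard error and an unadjusted SD. That is correct; they are illustrations, and the identification problem does not depend on them.

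A reader might also infer more than the documents support:

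- **A negative expected increment.** Subtracting TASMINH2's 5.4 mm Hg from the hypothesised 5 mm Hg gives −0.4. But 5 is a planning target based on that same trial, not a forecast relative to it.
- **A different population or period in TASMINH2.** The article describes neither.
- **A fault in the process question** "Does the inclusion of lifestyle change choices and behavioural support result in engagement with lifestyle change". This asks about engagement and claims no added effect on BP or cost-effectiveness.
- **A contrast of everything against nothing.** Additional support is optional, lifestyle choices open at nine weeks, and controls also receive a medication review.

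**Conclusion.** The statement in the Economic analysis section is wrong as written. The trial tests the combined package against usual care and does not identify the added value of behavioural support. The related aim in the Economic analysis plan can be met only with external, non-randomised evidence on the comparator. With SD 17, 244 per arm and an assumed external standard error of 1.0 to 2.0, a cross-trial difference would carry a 95% interval of about ±3.6 to ±4.9 mm Hg before any gain from baseline adjustment. That is too imprecise to separate a modest added benefit from none.

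Severity is moderate. It would be tempting to conclude that the trial's main result or its economic comparison with usual care is compromised. The documents do not support that, because both rest on the randomised contrast.

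**What to change.** - **Economic analysis.** Replace the claim with a statement that the trial tests the combined, digitally delivered package against usual care.
- **Economic analysis plan.** Keep HOME BP against usual care as the base case. Present the added-element result as an exploratory, non-randomised indirect comparison through usual care. Name the source of the comparator effect, state the assumption that the two trials are similar enough to compare, and propagate sampling error from both sources.
- **Reference intervention.** Reconcile the paper-based comparator with the tele-monitoring connection described for TASMINH2, and say that the contrast also takes in the differences in medication-change recommendations, recording and reminders.

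The cost is some rewording, one extra probabilistic analysis and a less ambitious secondary economic claim. The design and sample size do not change.

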#### Economic analysis plan

A within trial analysis will estimate cost per unit reduction in SBP, the primary outcome, with adjustments in that outcome as described in the ‘Statistical analysis’ section, including subgroups. Costs will include those due to the intervention, as well as those due to changes in medication, use of other relevant NHS resources and any costs borne by patients such as in diet and lifestyle. NHS and societal costs will be estimated and uncertainty explored in sensitivity analyses. To facilitate analysis of the difference between the intervention in HOME BP and that of self-management, the components and the cost of the intervention in HOME BP will be compared with that of TASMINH2.

These short-term results will provide input to a long-term cost-effectiveness model, based on that developed for TASMINH2, updated by subsequent work as relevant. Since these studies all show reductions in BP as cost reducing or highly cost-effective, this modelling will address the cost-effectiveness of the HOME BP-intervention versus usual care but also of the addition of the behavioural/digital element relative to paper-based self-management without that element. The HOME BP trial will collect data on numbers and types of antihypertensive prescriptions between arms.

### Qualitative substudy

The qualitative interviews will seek to provide an in-depth understanding of the factors that may facilitate or diminish the acceptability of the HOME BP intervention, and adherence to implementation from the perspective of patients and healthcare professionals using HOME BP. Interviews and focus groups will be undertaken alongside participation and after participants finish the HOME BP intervention for patients in the intervention and usual care groups. Purposive sampling will be used to select patients from the intervention group by age, gender, socioeconomic status and level of engagement with the website to allow for a wide range of views and experiences of the HOME BP online and the HOME BP intervention. Open-ended inductive questions will be used to elicit user perspectives and experiences of the intervention and the support provided, allowing participants to freely describe their experiences and views in their own way and to focus on whatever is most salient to them. Focus group discussions and interviews will also be conducted with healthcare professionals who have been involved in the trial procedures or intervention delivery. Interviews and focus groups will be audio-recorded, fully transcribed and analysed thematically.

## Ethics and dissemination

### Ethical approval

Ethical approval for the HOME BP study has been obtained from the South Central—Hampshire A Ethics Committee (reference: 15/SC/0082). R&D approvals have been obtained from all relevant Clinical Research Networks. All substantial amendments must be approved by the University Ethics Committee and NHS Ethics Committee responsible for the trial, in addition to approval by NHS R&D. Investigators are kept up to date with relevant changes via regular management group meetings.

### Data monitoring

The Programme Steering Committee is responsible for ensuring programme adherence to the protocol, and adherence to the requirements of the Guidelines for Good Clinical Practice. It was decided by the Steering Committee that a data monitoring committee was not required. The trial may be subject to inspection and audit by University of Southampton, under their remit as sponsor, the trial coordinating centre as the Sponsor's delegate and other regulatory bodies.

### Dissemination

Dissemination of our research will be via multiple pathways. We will submit the primary, secondary and tertiary study results for publication in highly cited and open access peer-reviewed journals and present findings at national and international conferences. We will also provide summaries of HOME BP findings to professional societies (such as British Hypertension Society), patient groups (Blood Pressure UK), participants, NHS organisations and healthcare providers. We will also disseminate to the public through regular press releases and to stakeholders through interactive workshops.

If cost-effective, the HOME BP intervention will be disseminated for clinical use by University of Southampton or a suitable, appropriate licensed partner. Following the Behavioral Intervention Technology model,^51^ we anticipate that future technology enhancements in mode of delivery of the intervention will be possible and desirable without the need to re-evaluate the essential behaviour support content of the intervention. For example, as smartphone use becomes more prevalent in the target population it will be easy to transfer the content of HOME BP for delivery by smartphone, with automatic transfer of BP readings (which will reduce the potential for patient error).
